### Pilot study

A pilot study was conducted from January 2014 in Germany and February 2014 in Ireland and Italy, with sites having been pre-randomised to the intervention or control (see below). This pilot was used to identify problems with the research design and trial processes, to refine data collection and to examine selection and enrolment processes. The pilot concluded in March 2014 in Ireland and in April 2014 in Germany and Italy. The main analysis for OptiBIRTH will exclude women recruited during the pilot trial. It will include data on women who gave their consent on or after 1 April 2014 in Ireland and 1 May 2015 in Germany and Italy.

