## Discussion

Recruitment to the OptiBIRTH trial is expected to close in all sites in 2015, with all participating women expected to birth by the end of the year. Recruitment has been slower than anticipated, in part because birth rates have fallen at several of the sites. As with cluster randomised trials in general, it has not been possible to recruit all potentially eligible women at each site. Among the reasons for this are that some of the women who were offered participation in the trial did not wish to join and because of challenges in fully initiating the study in each site. This may introduce differences between the participants in the intervention and control sites, which reinforces the importance of the primary analyses being a comparison of the VBAC rates for all women with one previous caesarean section at each site before and after the study period using routine data from each site. If the OptiBIRTH intervention succeeds in increasing VBAC rates, its application across Europe might avoid 160,000 unnecessary caesarean sections every year, which occur at an extra direct annual cost of more than €150 million.

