## Trial status

This protocol was submitted for publication in May 2015 when recruitment was ongoing. The last women are expected to join the trial by October 2015.

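### The consent cut-off for Germany and Italy is a year later than the end of their pilot, so the written rule drops about two thirds of their main-phase recruitment period

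*Protocol article*

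**What the plan says.** All the statements that conflict are in the protocol article, section Pilot study.

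- Start of the pilot: "A pilot study was conducted from January 2014 in Germany and February 2014 in Ireland and Italy".
- End of the pilot: "The pilot concluded in March 2014 in Ireland and in April 2014 in Germany and Italy".
- Purpose of the exclusion: "The main analysis for OptiBIRTH will exclude women recruited during the pilot trial".
- Resulting analysis set, by date of consent, starting from: "1 April 2014 in Ireland and 1 May 2015 in Germany and Italy".

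Two later statements fix the other end of the recruitment window. Trial status says "The last women are expected to join the trial by October 2015", and the Discussion describes recruitment closing in 2015, "with all participating women expected to birth by the end of the year". Trial status also says "This protocol was submitted for publication in May 2015 when recruitment was ongoing".

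**The concern.** The only reason given for a consent-date limit is to keep pilot women out. For Ireland the limit does exactly that. For Germany and Italy it also removes every woman who consented from 1 May 2014 to 30 April 2015, after the pilot had ended. The stated purpose and the stated date cannot both hold.

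The date matters because it is the article's only consent-date rule for the analyses of recruited women and their babies described under Data analysis. Those analyses cover all the secondary maternal and neonatal outcomes, including rare harms such as uterine rupture and maternal or neonatal death, together with the covariate-adjusted analyses and the subgroup analysis by country. An analyst who followed the text would lose most of the German and Italian information on these outcomes.

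If the trial instead used 1 May 2014 without saying so, it would depart from its published analysis set by a year in two countries. The Randomisation section says that women are recruited after allocation is known, and that this knowledge may have influenced recruitment. In that setting an unexplained change to the analysis set is hard to defend later.

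**Working it through.** **1. Reproduce the cut-offs.** Rule: cut-off = first day of the month after the pilot ended.

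| Country | Pilot ended | Cut-off implied | Cut-off printed | Difference |
|---|---|---|---|---|
| Ireland | March 2014 | 1 April 2014 | 1 April 2014 | 0 days |
| Germany, Italy | April 2014 | 1 May 2014 | 1 May 2015 | 365 days |

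The rule reproduces the Irish date. It misses the other date by exactly one year.

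**2. Look for an explanation elsewhere.** No section mentions a second pilot, a suspension of recruitment or a late main phase in Germany or Italy. Study setting points the other way. It reports that a German site was withdrawn after recruiting nobody in its first 6 months. Counted from the German pilot start in January 2014, that period runs to June 2014, beyond the pilot's end. Counted from 1 May 2015, it would end only when recruitment was due to close, yet the article was submitted in May 2015.

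**3. Time lost in Germany and Italy.** It is unclear whether recruitment by October 2015 means closing at the end of September or of October, so both are shown.

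| Recruitment closes | Window from 1 May 2014 | Window from 1 May 2015 | Lost |
|---|---|---|---|
| 31 October 2015 | 549 days (about 18 months) | 184 days (about 6 months) | 365/549 = 66% |
| 30 September 2015 | 518 days (about 17 months) | 153 days (about 5 months) | 365/518 = 70% |

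Ireland keeps its full 18 to 19 months.

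**4. Illustrative share of women lost.** The article gives no monthly or country counts, so this step needs an assumption: every cluster recruits equally per month. The 16 sites form 15 clusters (5 Irish, 5 Italian and 5 German, two German units in one city being counted as one). Ten clusters are therefore affected, or nine if the withdrawn German site was a cluster of its own.

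- Closing in October, 10 clusters: total 5 × 19 + 10 × 18 = 275 cluster-months; lost 10 × 12 = 120; 120/275 = 44%.
- Closing in October, 9 clusters: total 95 + 9 × 18 = 257; lost 9 × 12 = 108; 108/257 = 42%.
- Closing in September, 10 clusters: total 5 × 18 + 10 × 17 = 260; lost 120; 120/260 = 46%.
- Closing in September, 9 clusters: total 90 + 9 × 17 = 243; lost 108; 108/243 = 44%.

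**5. Sensitivity to unequal recruitment** (October close, 10 clusters; the factor of two is my assumption).

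- Irish clusters recruit twice as fast: 120/(190 + 180) = 32% lost.
- Irish clusters recruit half as fast: 120/(47.5 + 180) = 53% lost.

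Ireland's share of the women who remain is 95/155 = 61% with equal rates, 190/250 = 76% with the doubled rate and 47.5/107.5 = 44% with the halved rate. With equal rates and no date error it would be 95/275 = 35%.

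**The case against.** The strongest reply is that this is a one-digit slip that the paragraph itself allows a reader to repair. The pilot end months and the purpose of the exclusion stand immediately before the date, and the Irish date shows the pattern. An analyst would probably see the intended year, and correcting it would restore a rule already stated rather than create a new choice. This is the likeliest explanation, and it weakens the fear that a year of data would really be thrown away. It does not make the written rule correct, because the date is the operative part of an analysis-set definition.

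Second, the primary result is untouched. This is right. The primary outcome is the site-level VBAC rate among all women with one previous caesarean section, taken from routine data and comparing 2012 with a period after the last trial birth. A consent date cannot alter it. The damage is confined to the analyses of consenting women, although the Pilot study section calls the affected analysis the main one.

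Third, the share of women lost is not known. Sites range from 2,000 to 8,500 births a year and start-up was uneven, so equal recruitment is only a working assumption. This stands: the loss of calendar time is firm, the loss of women is illustrative, and whether the remaining sample would be mostly Irish depends on country-specific recruitment.

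Fourth, the SAP is not shown and may already carry the right date. That is also fair, and it limits what can be asked of the SAP to a check.

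**Conclusion.** The concern holds. The Pilot study section contradicts itself, and the date for Germany and Italy is wrong as written, by exactly 12 months against the article's own pilot end and exclusion rule. Followed literally, it removes 365 days, or 66% to 70%, of the post-pilot recruitment window in two of three countries. With equal recruitment per cluster-month this is 42% to 46% of all main-phase women; a twofold difference in Irish recruitment either way widens that to about 32% to 53%.

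The conclusion rests on two inferences: that women did consent in Germany and Italy between May 2014 and April 2015, which ongoing recruitment implies but no count confirms, and that no unreported pause occurred. It concerns the secondary, safety, adjusted and subgroup analyses of consenting women, not the site-level primary comparison.

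**What to change.** Change the year in the cut-off for Germany and Italy so that it reads 1 May 2014, and publish this as a dated correction before the data on consenting women are compared by arm. If the later date was intended, state the reason and reconcile it with the pilot end dates and the exclusion rule. Check that the SAP and the data-extraction rules use the same date. It would help to report, by country, how many women consented between 1 May 2014 and 30 April 2015, so that readers can see what the date governs. The cost is one date and a short correction notice; no new data are needed.

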### Randomisation

The unit of randomisation in the trial is the maternity unit (the ‘site’). Randomisation had to be done in advance of recruiting women to participate in the trial to allow appropriate preparations to be made in each site. Further, given the temporal nature of pregnancy, it is not possible to hold randomisation until all women in each participating site have been recruited, because some women would have given birth by the time the last woman would have been recruited. However, as with cluster trials in which the participants cannot be blinded to the intervention, once the sites had been randomised, it is possible that recruitment of women to the trial was influenced by the knowledge of whether or not they would receive the OptiBIRTH intervention at that site. Hence, the primary analyses for the trial (see below) will consider data at the level of each site as a whole, rather than at the level of the women who were approached and formally recruited.

Within each of the three countries, the maternity units were matched by their annual number of births and then by VBAC rate. They were matched in either pairs or triplets and then randomised 1:1 or 2:1 to intervention or control, respectively. The randomisation was done using the random number generator in Microsoft Excel [RAND], with the first site in each matched pair or triplet being assigned a random number between 0 and 1. If the number was below 0.500, the site was allocated ‘OptiBIRTH intervention’. If it was above 0.500, the site was allocated ‘control’. If the number had been exactly 0.500 the randomisation would have been done again, but this did not happen. Where a matched pair had been formed, the second site was automatically allocated the opposite of the first site. Where a matched triplet had been formed, if the first site was allocated to the control group, the other two sites were automatically allocated to the intervention group. If the first site was allocated to the intervention group, the randomisation was repeated for the second site, and the third site was automatically allocated to the opposite of the allocation for the second site.

The randomisations were done in the presence of a witness who was unaware of which site was associated with which code within the pairs and triplets until after the allocations were complete. Although we recognise that it is not possible to mask the allocation of the sites from people who are familiar with them, including pregnant women and practitioners, further information on the sites is not included in this published protocol, to reduce the possibility that this knowledge might influence the referral of pregnant women to the participating sites during the recruitment phase for the trial or the follow-up period for the primary outcome analysis (see below).

### Eligibility criteria for participants

To be eligible for inclusion, pregnant women at a participating site must meet the following criteria:Be ≥18 years of age at the time of bookingHave had one previous caesarean section using a lower segment transverse incision (not a classical/high vertical incision)Speak and understand a language for at least one of the trial countries (English, German or Italian)Provide informed consent to participate in the study

If a woman is known to have a multiple pregnancy at the time of the booking, she is not eligible.

### Training and support for trial sites

Staff members at all study sites are proficient in maternity care provision and in caring for women with one previous caesarean section. They are provided with information on the trial by members of the research team, including the national postdoctoral researchers and principal investigators.

### Interventions

Participating sites were randomised to either intervention or control.

#### OptiBIRTH intervention

Sites randomised to the intervention group will receive a complex innovative programme of evidence-based antenatal strategies, incentives and activities to increase the empowerment, engagement and involvement of women with a history of one previous caesarean section. Full details of the OptiBIRTH intervention will be published in a separate paper but, in summary, it seeks to empower women and to develop a community of practice in the site, with the intention of increasing the VBAC rate. The package includes face-to-face educational sessions about VBAC for clinicians in each site, specially designed antenatal classes for the recruited women and an optional interactive website and applications, which will assist them in setting personal goals to achieve their optimal birth outcome. Building a community of practice at the site, which would be more favourable to VBAC, should impact all women at the site, not just those who attend the antenatal classes or access the online resources.

#### Control

Sites randomised to the control group will receive the current standard of care in that maternity unit.

### Process evaluation

The OptiBIRTH research team has developed a process evaluation plan to explore and document the implementation of the OptiBIRTH intervention, and how it was received by key stakeholders and to identify factors that could explain variation in outcomes across intervention sites. This evaluation will include details of the attendance of clinicians at their face-to-face educational sessions, the attendance of women at the antenatal classes and their use of the online resources. It will also include the gathering of information from both clinicians and women on their experiences with the OptiBIRTH intervention and the various activities and resources made available to them. In addition, the sites in which the intervention was implemented will be described, and findings will be used to assist in interpretation of the trial results. Such process evaluations are particularly important in cluster randomised trials, where a ‘standardised’ intervention may, in fact, be implemented in different ways or be the subject of different reactions [31]. A resulting ‘lack of effect’ may thus merely indicate problems with implementation rather than true ineffectiveness [8].

### Outcome measures

#### Primary

The primary outcome measure will be the VBAC rates for women with one previous caesarean section for each site comparing the years before and after the delivery of the intervention. This is calculated as the number of women who gave birth by spontaneous vaginal delivery or with the use of ventouse or forceps after a single previous caesarean section, divided by the total number of women who gave birth at the site after a single previous caesarean section.

#### Secondary

Secondary maternal outcomes collected at and shortly after birth are described below:Use of health care and other resourcesLabour onset (spontaneous, induced, etcetera)Spontaneous rupture of membranesAcceleration of labour (artificial rupture of membranes, oxytocin use)Analgesia during labourLength of labourMode of birthPerineal trauma (1st, 2nd, 3rd, 4th degree tear; episiotomy)Maternal morbidity (for example: post-partum haemorrhage, uterine rupture, wound breakdown, admission to intensive care unit, etcetera)Maternal deathLength of postnatal hospital stay (days)

Secondary neonatal outcomes collected during pregnancy and at, and shortly after, birth are described below:Fetal demise during pregnancy (miscarriage, stillbirth, intrauterine death)Gestation at birthApgar scores at 1 and 5 minutes after birthUmbilical arterial and venous cord pH and base excessNeonatal resuscitationAdmission to neonatal intensive care unitNeonatal mortalityNeonatal morbidity (for example: seizures, hypoxic-ischemic encephalopathy, intracranial haemorrhage, meconium aspiration syndrome, renal failure, etcetera)Length of neonatal postnatal stay (days)

Secondary maternal outcomes collected at 3 months post-partum are described below:Satisfaction (with the intervention, mode of birth and participation in trial)Breastfeeding (initiation and over the first 3 months post-partum)Quality of life (measured by SF-36)Use of health care and other resources

### Sample size assumptions and estimates

The sample size for this cluster randomised trial was derived by adjusting an estimate for the sample size for an individually randomised trial to allow for clustering. This was done by inflating the estimate by the design effect given by 1 + (ñ-1)ρ, where ñ is the average cluster size and ρ is the estimated intra-class correlation coefficient (ICC) for this study. With a background proportion of successful VBAC of 25 % and an ICC of 0.05, 12 trial units would be required, each containing 120 participating women (840 women in the intervention group and 840 women in the control group), to detect a 15 percentage point difference in successful VBACs (that is, an increase from 25 % in the control group to 40 % in the intervention group), with power of at least 80 % and an alpha level of 0.05. If the true ICC values are less than 0.05, the power of the study will increase. To allow for a loss to follow-up of 20 % of women and the possibility that one site per country will drop out of the trial, 15 trial units (16 maternity sites) were randomised across three countries.

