### Data analysis

Statistical analysis plans will be prepared for the analyses of both the clinical and the cost-effectiveness data, and made available separately to this protocol. Where possible, the main analysis will be by ‘intention-to treat’ but this is not always possible in a cluster randomised trial where, by the nature of the intervention, the recruiters and the potential participants are aware of their allocated intervention before they are asked to provide their consent. Therefore, the principal analysis to test the effect of the intervention at the site level will compare differences in the primary outcome, namely the proportions of VBAC, between the intervention and control sites. The comparison of VBAC rates in each of the participating sites will compare the change in the VBAC rates in the intervention sites versus the change in the control sites between the calendar year 2012 (that is, before the OptiBIRTH intervention was available to any hospital) and, if possible, the 12-month period after the month that the last OptiBIRTH baby is born in each hospital. However, for some hospitals, it might be necessary to use the data for the calendar year (that is, January to December) that follow the birth of the last OptiBIRTH baby in that hospital because of the practical difficulties of accessing hospital level data for periods other than calendar years.

In addition to the primary analyses at the level of the hospital, we will analyse the data for the women who agree to take part in the trial and their babies, in order to assess the effects of the intervention on the secondary outcomes listed above. Where outcomes have been collected as continuous variables (for example, duration of labour) they will be analysed as continuous data to compare the intervention and control sites. Likewise, dichotomous data (for example, breast feeding at 3 months) will be used to compare the proportions in the intervention and control sites. The analyses will adjust for whether the woman had had any prior vaginal birth or prior VBAC, and her BMI and age. We will conduct subgroup analyses for these adjustment variables and the three countries. Our hypothesis is that the effects of the intervention will not be so heterogeneous across these subgroups to invalidate the calculation of an overall result for the trial as a whole.

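### The sample-size sentence does not add up (12 × 120 is 1,440 women, not 1,680), and 12 units miss the stated 80% power whether alpha is one- or two-sided

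*Protocol article*

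**What the plan says.** All the figures come from the protocol article, section Sample size assumptions and estimates, unless another section is named.

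- Method: "This was done by inflating the estimate by the design effect given by 1 + (ñ-1)ρ, where ñ is the average cluster size".
- Inputs: "With a background proportion of successful VBAC of 25 % and an ICC of 0.05"; the effect is "an increase from 25 % in the control group to 40 % in the intervention group".
- Result: "12 trial units would be required, each containing 120 participating women (840 women in the intervention group and 840 women in the control group"), for a power of no less than 80% at an alpha of 0.05. Whether alpha is one- or two-sided is not stated.
- Reserve: to cover 20% loss of women and the drop-out of one site in each country, "15 trial units (16 maternity sites) were randomised across three countries".
- Allocation (section Randomisation): units were matched in pairs or triplets and "randomised 1:1 or 2:1 to intervention or control, respectively".
- Primary analysis (section Data analysis): it will "compare the change in the VBAC rates in the intervention sites versus the change in the control sites", from 2012 to a year after the last trial birth at each hospital. Under Discussion, this is done with routine data on all women with one previous caesarean.

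**The concern.** Two counts in one sentence cannot both be true, and the stated power is attached to the pair. This is the article's only justification of the trial's size. If the claimed power is higher than the design delivers, a null result may be taken as stronger evidence against a 15-point effect than it is. The reserve of spare units and the assumption of equal arms rest on the same paragraph, so an error in the base count carries through to them.

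**Working it through.** **Inputs (all from the sample-size section):** p₁ = 0.25, p₂ = 0.40, ICC = 0.05, m = 120, alpha = 0.05, power 0.80.

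**1. Counts.** 12 × 120 = 1,440, i.e. 720 per group. The stated 840 + 840 = 1,680. 1,680 / 120 = 14 units; 1,680 / 12 = 140 women per unit.

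**2. Reproducing 840.** Individually randomised size per arm, pooled variance under the null:

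n = [z_α √(2p̄(1−p̄)) + z_β √(p₁(1−p₁) + p₂(1−p₂))]² / (p₂−p₁)², with p̄ = 0.325.

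Design effect = 1 + (120 − 1) × 0.05 = 6.95.

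- One-sided 0.05: n = 119.5; 119.5 × 6.95 = 831 per arm; 831 / 120 = 6.92, rounded up to 7 clusters, or 7 × 120 = **840 per arm**, 14 units.
- Two-sided 0.05: n = 151.9; 151.9 × 6.95 = 1,055 per arm (1,056 if n is first rounded up to 152); 1,056 / 120 = 8.8, rounded up to 9 clusters per arm, 18 units.

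So 840 and 80% agree with each other under a one-sided test with 14 units. The figure that does not fit is 12.

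**3. Power delivered.** Effective n per arm = women per arm / design effect. The ranges are for pooled and unpooled variance. The last column uses a t-test with (clusters − 2) degrees of freedom.

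| Design | Design effect | Effective n per arm | Two-sided | One-sided | Two-sided, t |
|---|---|---|---|---|---|
| 12 × 120 | 6.95 | 720/6.95 = 103.6 | 64–65% | 75–76% | 56% |
| 12 × 140 | 7.95 | 840/7.95 = 105.7 | 65% | 76% | 57% |
| 14 × 120 | 6.95 | 840/6.95 = 120.9 | 70–71% | 80–81% | 64% |
| 18 × 120 | 6.95 | 1,080/6.95 = 155.4 | 81–82% | 88–89% | 77% |

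Neither 12-unit design reaches 80%.

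**4. Reserve.** If 12 units are needed, 15 − 12 = 3 spares match one drop-out per country, and nothing is left for the 20% loss of women unless 120 is the number after loss. If 120 is the number recruited, loss of women alone leaves 15 × 120 × 0.8 = 1,440, and both losses leave 12 × 96 = 1,152. If 14 units are needed, 15 − 14 = 1 spare, not three.

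**5. Allocation.** Ireland and Italy each have five sites. Germany has six, two of which form one cluster (sections Study setting and Design). That is five clusters per country, which in pairs and triplets can only be one of each. The triplet procedure always yields two intervention sites and one control. Each country is therefore 3:2 and the trial 9:6. For 9:6 units of 120 (effective n 155.4 and 103.6), power is about 71–74% two-sided or 81–83% one-sided; with t on 13 df it is about 67% or 79%. Section Study setting also reports one German site withdrawn, without its arm.

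**The case against.** The strongest reply is that the article never says the test is two-sided. With a one-sided alpha of 0.05, its formula gives 840 per arm and just over 80% power, so the sentence may contain no more than a wrong unit count. That stands. A reader might infer that the article's own formula yields 65–71% and that its 80% is simply false; the documents do not support that as an unconditional statement. It is true of 12 units on either reading, but of 14 units only if the test is two-sided. Two-sided is, however, the usual reading of an unqualified alpha.

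A reader might also infer that the primary analysis is underpowered. That is not shown either. Its power depends on the number of women per site-year and on the correlation between a site's rates in the two periods. The article gives neither, plausible values fall on both sides of 80%, and the separate analysis plan may address it.

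Two further limits hold. The text can be read as 120 women per unit after loss, in which case the 20% is met by recruiting more per unit. And the 9:6 split is the one randomised; unless the withdrawn German site was half of the combined cluster, 14 units remain, at 8:6 or 9:5.

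Finally, recruitment was nearly complete when the article was submitted, so a correction changes no conduct. It still changes what a reader is told about the power.

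**Conclusion.** The paragraph is wrong as written. Its unit count and its women per group differ by 240 women (1,680 − 1,440), or two units of 120, and 12 units of 120 give about 64–65% power two-sided or 75% one-sided against a stated minimum of 80%. The contradiction in the counts needs no assumption. The power figures rest on the article's own effect, ICC and design effect, with a normal approximation; a t-test on cluster degrees of freedom lowers them.

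The stated 840 per group and 80% hold together only for 14 units and an unstated one-sided alpha of 0.05. On the two-sided reading, 14 units of 120 have about 70–71% power (64% with t). In either case the 15 randomised units do not clearly provide the two reserves claimed for them, and the equal arms in the calculation are not the arms that were randomised. The whole calculation concerns participating women at follow-up, so it does not describe the power of the site-level comparison of change that is primary.

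**What to change.** Revise the one paragraph:

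1. Give one consistent set of units, women per unit and women per arm.
2. State whether alpha is one- or two-sided. If it was one-sided with 14 units, change 12 to 14 and say so. If two-sided, withdraw the 80% claim.
3. State the power delivered under that choice with the actual allocation. For 15 units at 9:6 with 120 women each, this is about 71–74% two-sided or 81–83% one-sided by normal approximation. It is lower with a t-test, and lower again if the withdrawn German site cost a cluster.
4. Say whether 120 is before or after the 20% loss, and which losses the 15 units cover.
5. Say that the calculation applies to participating women at follow-up, and not to the site-level change analysis.

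The cost is a paragraph of wording and, on the two-sided reading, a less favourable stated power. No additional women or sites are needed.

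### The sample size section gives two different trial sizes, and 12 units of 120 women reach about 64 % power two-sided or 75 % one-sided, not the stated 80 %

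*Protocol article*

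**What the plan says.** The section headed Sample size assumptions and estimates sizes the trial as an individually randomised one and then allows for clustering by "inflating the estimate by the design effect given by 1 + (ñ-1)ρ". The target is "to detect a 15 percentage point difference in successful VBACs", namely "an increase from 25 % in the control group to 40 % in the intervention group". The ICC is 0.05, alpha is 0.05 with no statement of one or two sides, and power is given as at least 80 %.

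The resulting size is "12 trial units would be required, each containing 120 participating women (840 women in the intervention group and 840 women in the control group"). The section adds that "If the true ICC values are less than 0.05, the power of the study will increase". It then allows for 20 % loss of women and for one site per country dropping out, and reports that 15 trial units were randomised.

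The sections Outcome measures (Primary) and Data analysis define the principal analysis differently. It compares intervention and control sites on the change in each site's VBAC rate, from calendar year 2012 to a period after the last trial birth, among all women at the site with one previous caesarean.

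**The concern.** The section publishes its formula, every numerical input, the size and the power, so it can be checked. Two things fail on a first pass. The number of units and the number of women in the same sentence do not multiply out. And an individual sample of roughly 150 per arm, inflated by a design effect near 7, comes to over 1,000 women per arm, well above either stated size.

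A stated power is what readers use to judge what a sample size could have shown. If it is overstated, the adequacy of the participant-level sample is overstated with it, and a reader cannot tell which size the figure belongs to.

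**Working it through.** **Inputs** (all from the sample size section): p₁ = 0.25, p₂ = 0.40, difference 0.15, ICC ρ = 0.05, alpha 0.05, power 0.80, design effect 1 + (m − 1)ρ with m = 120. Sidedness is not given, so both are shown.

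**1. The two sizes.** 12 × 120 = 1,440, or 720 per arm. 840 + 840 = 1,680 = 14 × 120 (or 12 × 140). Loss to follow-up does not bridge the gap: it is allowed for afterwards, in going from 12 to 15 units, and 720/0.8 = 900, not 840.

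**2. Trying to reproduce the stated size.** Mean proportion p̄ = 0.325, √(2p̄(1 − p̄)) = 0.6624, √(p₁(1 − p₁) + p₂(1 − p₂)) = 0.6538. Individually randomised n per arm = (z_α × 0.6624 + 0.8416 × 0.6538)² / 0.15².

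- Two-sided (z = 1.960): (1.2983 + 0.5503)² / 0.0225 = 151.9, so 152.
- One-sided (z = 1.645): (1.0895 + 0.5503)² / 0.0225 = 119.5, so 120.

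Design effect = 1 + 119 × 0.05 = 6.95.

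- Two-sided: 152 × 6.95 = 1,056 per arm; 1,056/120 = 8.8, so 9 + 9 units (2,160 women).
- One-sided: 120 × 6.95 = 834 per arm; 834/120 = 6.95, so 7 + 7 units, which is 840 per arm.

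The figure of 840 is therefore reproduced by a one-sided calculation with 14 units. Neither sidedness produces 12 units.

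**3. Power for each size.** Effective n per arm = women per arm / design effect. Power = Φ[(0.15√n_eff − z_α × 0.6624) / 0.6538].

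Example, 12 × 120: n_eff = 720/6.95 = 103.6. Two-sided: (1.527 − 1.298)/0.6538 = 0.35, power 0.637. One-sided: (1.527 − 1.090)/0.6538 = 0.67, power 0.748.

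| Size | Design effect | n_eff per arm | Two-sided | One-sided |
|---|---|---|---|---|
| 12 × 120 (720 per arm) | 6.95 | 103.6 | 63.7 % | 74.8 % |
| 14 × 120 (840 per arm) | 6.95 | 120.9 | 70.4 % | 80.4 % |
| 12 × 140 (840 per arm) | 7.95 | 105.7 | 64.5 % | 75.5 % |
| 15 × 120, no loss | 6.95 | 129.5 | 73.4 % | 82.7 % |
| 15 × 96, 20 % loss | 5.75 | 125.2 | 72.0 % | 81.6 % |
| 18 × 120 | 6.95 | 155.4 | 80.9 % | 88.4 % |

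The 15-unit rows use 7.5 units per arm; a split of 8 and 7 gives the same 73 % two-sided with no loss.

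**4. Sensitivity to method.** For 12 × 120, two-sided power is 64.6 % with unpooled variance, 64.0 % by arcsine, 57.9 % with continuity correction and 55.9 % with a t-test on 10 degrees of freedom. The highest one-sided value for 12 × 120 is 75.5 % (unpooled). No variant reaches 80 %.

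**5. What would give two-sided 80 %.** Setting n_eff = 151.9 and solving for ρ: (720/151.9 − 1)/119 = 0.031 for 12 × 120, and (840/151.9 − 1)/119 = 0.038 for 14 × 120.

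**The case against.** The strongest reply concerns sidedness. The protocol says only that alpha is 0.05. If a one-sided test was meant, its formula gives 840 women per arm and 80.4 % power, so the number of women and the stated power agree. A reader might infer that the inputs cannot give 80 % at 840 per arm at all; that is too strong, and the 70 % figure rests on the conventional two-sided reading. What the reply cannot rescue is the 12 units: one-sided, the match needs 14, and 12 × 120 still gives only 75 %.

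A reader might also infer that no number of women per unit could rescue 12 units. As units grow, effective n per arm approaches 6/0.05 = 120. That falls short of the 152 needed two-sided (ceiling 70.1 %), but one-sided it just covers the 119.5 needed (ceiling 80.1 %). The absolute statement holds only two-sided.

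Second, 15 units were randomised, and 12 is what remains if one site per country drops out. This is fair, and the 15-unit figures belong in the account. They reach 80 % one-sided but remain at 72–73 % two-sided.

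Third, the calculation compares participating women after the intervention, whereas the principal analysis compares changes in site-level rates using routine data on all eligible births. This objection stands in full. It is tempting to conclude that about one trial in three would miss a true 15-point effect on the primary outcome. The document does not support that: power for the change in site rates depends on site-level numbers and on the correlation between periods, and neither is given.

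Finally, the remark that a smaller ICC raises power is true. It does not claim that 0.05 is a worst case, and it needs no correction.

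**Conclusion.** The point holds in this form. Two parts need no assumption beyond the section's own formula and inputs: the sentence states two incompatible sizes (1,440 and 1,680 women), and 12 units of 120 miss 80 % under either sidedness, by about 16 percentage points two-sided and 5 one-sided. A third part is conditional: with 840 per arm in 14 units of 120, power is about 70 % if the test is two-sided and 80 % if it is one-sided. That a one-sided calculation lies behind the 840 is a plausible inference from the close match, not something the protocol says.

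The figures rest on the normal approximation with pooled variance, equal unit sizes and a comparison of two proportions after the intervention. They say nothing firm about the power of the primary before-after analysis of site rates.

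**What to change.** Revise the sample size section as follows.

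- State whether alpha is one- or two-sided.
- Give one size in which units and women agree: 12 units with 720 per arm, or 14 units with 840 per arm.
- Replace the claim of at least 80 % with the power that the formula gives for that size. Two-sided, this is about 64 % for 12 × 120, about 70 % for 14 × 120, and about 72–73 % for the 15 units randomised. If useful, add that two-sided 80 % would need about 1,056 women per arm (9 + 9 units), or an ICC of at most about 0.031 (12 × 120) or 0.038 (840 per arm).
- Say that the calculation refers to a post-intervention comparison of participating women and is not the power of the primary comparison of changes in site-level VBAC rates.

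The cost is wording only. Recruitment, conduct and analysis are unchanged. On the two-sided reading, the stated power becomes less favourable.
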